### Participants

#### Inclusion criteria

The inclusion criteria are children with a burn injury who are managed in the acute phase post burn (up to 16 years of age, as per current practice) or who receive burn scar reconstructive surgery (up to 18 years of age, as per current practice) at the participating burns centre and who require attendance at a scar management clinic after skin healing. Children who receive skin grafting, children with wounds that have not healed by day 17 post burn and children receiving surgery for burn scar reconstruction in all body locations with a TBSA burned of less than or equal to 40% who are accompanied by a parent or guardian, who is able to provide informed consent, will be eligible for inclusion. Up to two scar sites per person will be recruited where possible with both sites receiving the same intervention. Children with a cognitive impairment that impedes their ability to communicate will be enrolled in the study, however, they will not be required to complete self-report measures. Children and their families who do not speak English will be approached to participate in the study with the use of an interpreter but will only have objective scar measures and the itch Numeric Rating Scale (NRS) administered.

#### Exclusion criteria

Exclusion criteria include children whose burns wounds have healed spontaneously within 16 days and who have not been referred for scar management; children with isolated facial or ear burns; children with isolated genital burns; children with comorbidities that might influence the primary outcomes (such as a dermatological disorder); children who are referred to their local health service before scar management is commenced and children involved with the Department of Communities (Child Safety) where the burns consultant and/or burn team members consider study involvement to be contraindicated.

### Intervention

Participants will receive standard care for the acute burn injury as determined by the burns multidisciplinary team. If a participant is recommended for scar management and their caregiver provides consent to participate, baseline assessment will be completed. Participants will then be randomly allocated into one of three scar management intervention groups according to the contents of the sealed envelope opened by an independent party. Group 1 will receive medical use topical silicone gel (Strataderm®). Group 2 will receive pressure garment therapy (Therapeutic Support Laboratory) only. Group 3 will receive a combination of topical silicone gel (Strataderm®) and pressure garment therapy. The intervention products will be provided to the patient as per standard practice once the skin is healed (e.g. sufficient topical silicone gel will be provided to allow coverage of the scar area until the next appointment and two sets of pressure garments will be provided to each child participant at a new fitting).

The study follow-up time periods will match standard occupational therapy review times (e.g. 3 months and 6 months post burn).

### Procedures

It is anticipated that data collection will take approximately 20 min at baseline, 3 and 6 month post burn or burn scar reconstruction appointments. It is expected that data collection will not exceed 10 min at the 1-week follow-up point.

### Outcome measures

#### Primary outcome measures

Scar itch intensity and scar thickness will be measured as primary outcomes. *Itch intensity* will be self-reported for children aged 5 years and older using an 11-point NRS (0 to 10). The Toronto Pediatric Itch Scale is an observation-based scale rating itch behaviours on a scale of 0 (absence of itch) to 4 (severe itch with significant disruption) and will be completed by caregivers for children aged under 5 years [20]. Caregivers for children of all ages will also complete the itch item of the Patient and Observer Scar Assessment Scale (POSAS, 0 to 10 NRS). Numeric rating scales have been recommended over visual analogue scales due to improved adherence, increased responsiveness and fewer missing values in populations of adults with pain and chronic itch [34, 35]. Numerical testing will be conducted with all children aged under 8 years and any children known to have learning difficulties to ensure they have the capacity to use the NRS [36].

*Scar thickness* will be measured using the GE Healthcare ultrasound. The GE Healthcare ultrasound system has been found to have an intraclass correlation coefficient (ICC) of greater than 0.90 for test-retest reliability when used with children with burn scars [37]. When measuring scar thickness with the GE Healthcare ultrasound, an image will be taken centrally from the site of interest (as opposed to peripherally on the scar border). An average of three measurements will be recorded and used in the analysis.

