### Objectives

This study aims to determine the effectiveness of topical silicone gel versus pressure garment therapy versus combined topical silicone gel and pressure garment therapy, in the prevention and management of burn scars in children aged 0 to16 years post burn or 0 to18 years post burn scar reconstruction. This will be investigated using the primary outcomes of scar itch and thickness at 6 months post burn or burn scar reconstruction. Current medical literature has been unable to demonstrate one treatment group as being superior to the others; however, we hypothesise that there will be at least one pairwise difference between the group means for scar thickness at the 6-month endpoint.

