### Statistics

#### Sample size

The sample size estimate was calculated based on the primary outcome of scar thickness at 6 months post burn for one scar site. We assumed a pooled standard deviation of 1.0 mm based on a retrospective audit of data from our centre. To detect a statistically significant between-group difference of 0.76 mm in scar thickness with 80% power and an alpha value of 0.017 (due to three pairwise comparisons), 36 participants are required in each of the three groups. Assuming a 20% dropout, the total number of participants who need to be recruited at baseline is 135 (45 participants per group).

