The primary outcomes will be analysed using mixed effects regression analyses to examine differences at 6 months post burn, adjusting for the baseline value of the outcomes. Mixed effect regression analyses will be completed for each follow-up time point. Potential confounding variables that are identified as imbalanced between the groups will be entered into regression analyses. The time-varying covariates are patient adherence, level of pressure beneath garments, and other interventions received. All of the other potential confounding variables are non-time-dependent covariates. Sensitivity analyses will be completed for missing data using multiple imputation of missing observations by creating ten complete data sets [49] of missing dependent and independent data. For participants from whom data is collected from two scar sites, the multiple sites on these individuals will be accounted for in analytic models by including the scar site as a random effect nested within participant. Initially all participants will be included in the analyses. The analyses will then be repeated after stratifying by surgical intervention (i.e. skin grafting in the acute phase, spontaneous skin healing in the acute phase, post-acute reconstructive surgery). Subsequently, the influence of sociodemographic, clinical and intervention factors, and primary and secondary outcomes not included as dependent variables, on primary and secondary outcomes will also be examined using regression models. Differences in health-related quality of life between the intervention group and respective normative comparison groups will be analysed using *t* tests, z-scores, or equivalent nonparametric tests where appropriate. Differences in self-reported outcomes by children versus caregivers, between age groups and in comparison to normative data will also be examined using univariate statistics such as *t* tests, z-scores, or nonparametric equivalents. Significance will be set at less than 0.05. Data will be analysed using SPSS (SPSS Inc., Chicago, IL, USA) or Stata (StataCorp, College Station, TX, USA) where appropriate.

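### Itch and thickness are both primary at 6 months, but the 0.017 allows only for three thickness comparisons and no rule links the two outcomes

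*Protocol article*

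**What the plan says.** In the protocol article, the section on primary outcome measures gives the two outcomes equal standing: "Scar itch intensity and scar thickness will be measured as primary outcomes". The Objectives section does the same and fixes the time point: "This will be investigated using the primary outcomes of scar itch and thickness at 6 months post burn or burn scar reconstruction".

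The next sentence of the Objectives narrows to one outcome: "we hypothesise that there will be at least one pairwise difference between the group means for scar thickness at the 6-month endpoint". No hypothesis is given for itch.

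The Sample size section also covers thickness alone: "The sample size estimate was calculated based on the primary outcome of scar thickness at 6 months post burn for one scar site". The target is a "between-group difference of 0.76 mm in scar thickness with 80% power", with an SD of 1.0 mm and "an alpha value of 0.017 (due to three pairwise comparisons". This leads to 36 evaluable children per arm, and 135 recruited after allowing for 20% dropout.

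The Data analysis section puts both primary outcomes through mixed effects regression at 6 months, adjusted for baseline. The only threshold it gives is general: "Significance will be set at less than 0.05". It does not repeat the 0.017, set an order of testing, or say whether one outcome or both must succeed.

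**The concern.** By sizing the trial at 0.05/3, the authors accepted that several primary comparisons need a stricter threshold. They counted three. With two primary outcomes and three arms there are at least six, and the 0.017 makes no allowance for the second outcome.

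This is separate from the mismatch between 0.017 in the sample size section and 0.05 in the analysis section. Changing the analysis threshold to 0.017 would protect thickness taken alone, but itch would still add three tests at the same level.

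At stake is what a primary result means. If thickness shows nothing and one itch comparison is significant, the article gives no basis for deciding whether the trial has succeeded. If that counts as success, the chance of a false success is higher than the 0.017 suggests.

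**Working it through.** **Inputs.** From the Sample size section: difference 0.76 mm, SD 1.0 mm, alpha 0.017, power 80%, 36 per arm, 20% dropout. From Study design: three arms, 1:1:1. From Data analysis: general threshold 0.05. Assumed: two-sided tests, one itch variable, either outcome sufficient for a claim. The correlation rho between itch and thickness is not given, so a range is shown.

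**Step 1. The plan's own figure.**
- n = 2 × [(z(1 − 0.017/2) + z(0.80)) × SD / difference]² = 2 × [(2.387 + 0.842) / 0.76]² ≈ 36.1 per arm. The stated 36 is reproduced; strict rounding up gives 37.
- A one-sided test would need 31, so the plan is two-sided.
- 36 / 0.8 = 45 per arm, and 3 × 45 = 135.
- Power with 36 per arm is 79.9% (normal) or 78.0% (t).

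The thickness sizing is sound.

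**Step 2. One outcome.** Simulation of three arms with all pairwise two-sided z-tests and no true differences (2 million runs) gives a chance of at least one false claim of 4.5% at 0.017 and about 12.2% at 0.05. So 0.017 does control one outcome.

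**Step 3. Two outcomes, six tests.** The same simulation with a second outcome correlated rho with the first:

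| rho | each test at 0.05 | each test at 0.017 |
|---|---|---|
| 0 | 22.9% | 8.8% |
| 0.3 | 22.4% | 8.6% |
| 0.5 | 21.3% | 8.2% |
| 0.7 | 19.6% | 7.7% |
| 0.9 | 16.7% | 6.4% |
| 1 | 12.3% | 4.5% |

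Hand check at rho = 0: 1 − (1 − 0.045)² = 8.8%, and 1 − (1 − 0.122)² = 22.9%. The Bonferroni ceiling at 0.017 is 6 × 0.017 = 10.2%.

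**Step 4. Cost of a six-way split.** Alpha = 0.05/6 = 0.0083.
- Normal power with 36 per arm: 0.76 / √(2/36) = 3.224; 3.224 − 2.638 = 0.586; Φ(0.586) = 72.1%, against 79.9% at 0.017.
- With t: 69.4%, against 78.0%.
- Restoring 80% (normal, unadjusted) needs 42 per arm. 42 / 0.8 = 52.5, so 53 per arm and 159 children.

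**Step 5. Gated testing.** For each pair of arms, test thickness at 0.017, and itch at 0.017 only if thickness is significant. Each pair is a fixed sequence with error at most 0.017. Over three pairs the total is at most 3 × 0.017 = 5.1%, whatever rho is. Alpha and power for thickness do not change.

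**The case against.** The strongest reply is that ordering and alpha sharing between two primaries often belong in a statistical analysis plan, which is not shown. The lack of such detail would not by itself be a finding. What stands is that the article fixes two primaries of equal status, sizes alpha for one of them, and sets 0.05 for the analysis. Following those statements gives the inflated rates above. A later plan that split alpha six ways would no longer match the power stated here.

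A second reply is that both outcomes might be required, or that the thickness-only hypothesis means thickness carries the confirmatory claim. Requiring both would not inflate the error, but no such rule is stated and power for itch would be unknown. The second reading is plausible, but it sits badly with calling itch primary.

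Three stronger readings are tempting, and the document does not support them:
- *The trial promises 5% error over all primary tests and breaks the promise.* No such guarantee is stated. The 0.017 appears only inside a thickness calculation.
- *Itch has no significance level at all.* The general 0.05 covers it. What itch lacks is any share of the adjusted alpha.
- *The false-claim rate is simply about 9%.* That is the independence case, and it presumes the analysis threshold has first been changed to 0.017.

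Two reservations about size also stand. Much of the 17% to 23% comes from the 0.05 threshold itself, since thickness alone at 0.05 already gives about 12%. The power loss in Step 4 ignores the planned baseline adjustment. Under the normal formula, a baseline correlation r with 1 − r² = 36/42, so r of about 0.38, would restore 80% at 0.0083. The document gives no such correlation, so this gain is possible but cannot be relied on.

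**Conclusion.** The concern holds in this form: two primary outcomes are named, the multiplicity allowance counts only thickness, and nothing says how the two are to be read together. If either outcome can support a primary claim, the chance of at least one false claim is about 17% to 23% under the stated 0.05. It would be about 6.4% to 8.8% if 0.017 were used throughout, for correlations from 0.9 down to 0. At 0.017 it falls to 4.5% only if the correlation is 1, which is hard to credit for reported or caregiver-observed itch against ultrasound thickness.

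These figures count itch as one variable. The article collects itch on a 0 to 10 self-report scale, a 0 to 4 caregiver-rated scale for under-fives, and a caregiver scar-scale item for all ages. Testing these separately would raise the rate further.

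The thickness sample size is not in question. The matter should be corrected, but it does not undermine the design.

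**What to change.** Make a dated amendment before data are analysed, in one of two forms:

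1. **Gate by pair.** For each pair of arms, test thickness at 0.017. Test one named itch variable at 0.017 only if thickness for that pair is significant. Put the same threshold in the Data analysis section.
2. **Single primary.** Name thickness the only primary outcome, with its three comparisons at 0.017, and itch the key secondary.

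Both agree with the stated hypothesis and keep the thickness power and the 135 children. Using 0.05/3 in place of the rounded 0.017 would bring the 5.1% bound to 5%.

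The text change is short, but the cost is more than wording. Recruitment began in August 2016, so the published outcome hierarchy would change during the trial, and the registration must be brought into line. A confirmatory itch claim would depend on thickness, although the Background argues separately for the importance of itch. Itch estimates and confidence intervals would still be reported in full. If the investigators want itch to stand alone, the alternative is the six-way split, with the power loss or the larger sample shown in Step 4.

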#### Secondary outcome measures

##### Scar severity

Scar severity will be measured using items of the *POSAS* including observer-scale items of thickness, vascularity, pliability, pigmentation and relief and patient scale items of itch, pain, colour, stiffness, thickness and irregularity. The POSAS has been found to be a reliable scar assessment and has the advantage of including a patient-report scale [8]. The POSAS observer scale has been found to have adequate test-retest reliability for pigmentation, pliability and overall opinion of the scar appearance in children [37]. Participants over the age of 8 years, caregivers and therapists will also complete a questionnaire regarding their overall opinion of the scar. The *DSMII ColorMeter* is an objective device that uses tristimulus reflectance colourimetry and narrow-band photometry to measure the lightness, redness or erythema, and pigmentation of a scar [4, 38]. The DSMII ColorMeter has been found to have an interobserver reliability ICC of 0.94 for lightness, 0.94 for erythema and 0.83 for pigmentation when used on scars [38]. At the participating burns centre, the DSMII ColorMeter has been found to have an ICC greater than 0.75 for immediate test-retest reliability on all scales when used with children with burn scars [37].

##### Health-related quality of life

The *Child Health Utility 9D* (CHU9D) (a preference-based utility measure) will be used to measure health-related quality of life and economic evaluation of the interventions. Items covered by the CHU9D include worry, sadness, pain, fatigue, annoyance, school work/homework, sleep, daily routine, and ability to join in activities. Preference weights from these are then converted to quality-adjusted life years for economic evaluation [39]. The CHU9D has been developed with, and validated for, use with children aged 7 to 17 years including validation with an Australian adolescent population [39]. The CHU9D and the *EuroQol 5D - Youth* (EQ5D-Y) have been found to have good levels of agreement (ICC = 0.80) in an Australian adolescent population [40]. Children will self-complete this assessment (from age 5 years) as able and a caregiver proxy report will be completed for children of all ages.

The *Brisbane Burn Scar Impact Profile* will be used to measure the intensity and frequency of sensations, such as pain, tightness and discomfort as well as health-related quality of life specific to people with burn scars. This measure was developed and tested for preliminary validity in children with burn scars and is undergoing further testing with children and caregivers [11]. In adults with burn scars the Brisbane Burn Scar Impact Profile has been found to have acceptable reproducibility, responsiveness and longitudinal validity ([name] et al. unpublished data).

##### Resource use and costs

*Resource use and costs* will be recorded for each participant from the perspective of the health service provider and costed at market rates. This will include trial interventions costs (e.g. the number and volume of topical silicone gel and pressure garment therapy products), as well as other burn-related resource use (and costs) that may be important to a health service deciding which of the interventions to implement in their model of care for patients with burns (e.g. moulds and splinting, overheads and labour time). Labour time (e.g. occupational therapists, physiotherapist, nurses and surgeons) will be quantified for each patient (on the basis of time duration utilised and number of appointments required) and costed at the relevant state award rates for each respective discipline.

##### Patient adherence

*Patient adherence* to wear and care regimes will be defined as ‘the extent to which a person’s behaviour coincides with medical or health advice’ [41]. Adherence will be measured using self-report questionnaires to child and caregiver participants, which will include questions about the number of hours per day of topical silicone gel and pressure garment therapy wear and reasons for nonadherence to interventions. The percentage of patient-reported nonadherence (using the actual hours of wear and recommended hours of wear) will be measured for each intervention group at the 3- and 6-month follow-up [42]. In addition, adherence will be measured and reported by the numbers of patients randomly assigned to each intervention, receiving the intended treatment, time to cessation of the intended intervention, completing the intended intervention as per the protocol, and analysed for the primary outcomes [42].

##### Treatment satisfaction

Treatment satisfaction has been reported to influence adherence to prescribed medical interventions [43, 44] and so is important to monitor over time. Treatment satisfaction will be measured using a caregiver and treating therapist self-report 0 to 10 NRS.

### Discontinuation/adverse events

The proposed interventions are considered to be part of standard care at the participating burns centre; therefore, minimal adverse events are expected. Known potential adverse events (e.g. a skin rash from topical silicone gel or skin damage from friction caused by pressure garments) have a standardised management protocol at the participating health service. Adverse effects of scar interventions will be monitored by reviewing patient medical records and by the self-report of caregivers, child participants (where appropriate) and treating therapists. All adverse effects will be reported to the clinical health service and the overseeing Human Research Ethics Committee. Discontinuation or alteration of treatment will be at the discretion of the treating clinical team and will be monitored throughout the study. At the conclusion of the study participants will receive standard care.

### Confounding factors

There are a number of potential confounding factors in this study. These include surgical intervention received (i.e. skin grafting in the acute phase, spontaneous skin healing in the acute phase, post-acute reconstructive surgery), patient’s adherence to the treatment regime, whether all essential elements of the intervention were delivered by treating therapists (therapist fidelity), the pressure beneath pressure garments, and/or adverse events impacting on the allocated treatment.

Patient adherence and therapist fidelity will be monitored via self-report checklists of salient elements of the intervention. Therapist fidelity will also be evaluated through the use of audio recordings of 20% of patient sessions [45]. Pressure beneath pressure garments will be measured in millimetres of mercury (mmHg) at the garment skin interface using the Pliance X device [46]. An ICC of 0.998 has been reported for static measures of test-retest reliability and an ICC of 0.995 to 1.00 has been reported for inter-rater reliability of the Pliance X device [47].

### Blinding

Baseline measures will be completed prior to randomisation. Due to the nature of the study double blinding will not be possible as treating therapists and patients and their families will be aware of the treatment modality. Investigator blinding will be difficult to maintain within this environment; therefore, the primary investigator will complete all outcomes measures without blinding. Ultrasound images and the measurement of burn scar thickness using the images taken by the primary investigator will be completed in real time at baseline, 1 week and 3- and 6-month follow-up points. However, at the conclusion of data collection a second investigator (blinded to the results during data collection and to the patient’s identity – nonidentifiable to the second investigator) will measure burn scar thickness using the ultrasound images taken by the primary investigator. Only the results of the blinded assessor will be used in data analysis. The inter-rater variation between the investigators will be reported for the study.

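### Blinding of scar thickness covers the reading of the ultrasound images but not their acquisition, which leaves a residual risk of bias of unknown size

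*Protocol article*

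**What the plan says.** All references are to the protocol article.

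- **Primary outcome measures** names the endpoints: "Scar itch intensity and scar thickness will be measured as primary outcomes". On placement it says that "an image will be taken centrally from the site of interest (as opposed to peripherally on the scar border", and that the mean of three measurements is analysed.
- **Blinding** says that baseline measures precede randomisation and that "the primary investigator will complete all outcomes measures without blinding". Imaging and the measurement of thickness from the images "will be completed in real time at baseline, 1 week and 3- and 6-month follow-up points".
- The same section then describes a second investigator, "blinded to the results during data collection and to the patient’s identity", who after data collection ends "will measure burn scar thickness using the ultrasound images taken by the primary investigator". It continues: "Only the results of the blinded assessor will be used in data analysis".
- It adds: "The inter-rater variation between the investigators will be reported for the study".
- **Data analysis** adjusts the primary outcomes for their baseline values.

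**The concern.** A thickness value is made in two steps: someone obtains an image, and someone measures it. The plan blinds the second step only. At 1 week, 3 months and 6 months, the person holding the probe knows the arm and sees the thickness value while the patient is still there. If the value looks unexpected, nothing in the described procedure prevents another image being taken and kept instead. The blinded reader sees only what was kept, so a shift already present in the images passes unchanged into the analysed values.

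This matters more for thickness than for other outcomes. The Objectives section states its hypothesis for thickness, and the Sample size section is built on it. The other primary outcome, itch, is reported by children or caregivers who know the treatment. Thickness is therefore the only primary outcome with any blinding, and readers will lean on it.

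**Working it through.** **1. The plan's own figure.** From the Sample size section: SD 1.0 mm, difference 0.76 mm, alpha 0.017 (taken as two-sided), power 80%.

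n per group = 2 × SD² × (z₁₋α/₂ + z₀.₈₀)² / δ² = 2 × (2.387 + 0.842)² / 0.76² ≈ 36.1

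This is 37 when rounded up, against 36 stated. With 36 per group, power is 79.9% by the normal approximation and 78.0% by the noncentral t. For dropout, 36 / 0.80 = 45 and 3 × 45 = 135, as stated. The sample size reproduces, and the point does not depend on it.

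**2. Which safeguards act on acquisition after allocation?**

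| Safeguard in the plan | What it protects | Does it remove a post-allocation acquisition shift? |
|---|---|---|
| Blinded second reading, used alone | Measuring on the image | No; it uses the same images |
| Central placement | Rules out the scar border | In part; it leaves some choice of spot, probe pressure and frame |
| Baseline before randomisation | The baseline image | No; later images are taken with the arm known |
| Adjustment for baseline | Chance imbalance and precision | No; the shift is absent from baseline |
| Inter-rater variation | Agreement between two readers | No; both read the same images |
| Test-retest ICC above 0.90 | Random error | No; it does not address error that depends on the arm |

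**3. Illustration of size.** The documents give no figure for an acquisition shift b between two arms, so b is an assumption.

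SE of a pairwise difference = SD × √(2/36) = 0.236 mm

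False-positive rate with no true difference = P(|Z + b/SE| > 2.387)

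| Assumed b (mm) | Share of 0.76 mm | False positive, normal | False positive, noncentral t | Power if b opposes a true 0.76 mm |
|---|---|---|---|---|
| 0 | 0% | 1.7% | 1.7% | 78% |
| 0.1 | 13% | 2.7% | 2.7% | 64% |
| 0.2 | 26% | 6.3% | 6.1% | 48% |
| 0.3 | 39% | 13.3% | 12.7% | 32% |

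The power column uses the noncentral t. If comparisons were tested at 0.05, the level given in the Data analysis section, the false-positive rates for 0.1, 0.2 and 0.3 mm would be 7.0%, 13.3% and 24.1% instead of 5%.

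**The case against.** The sponsor can fairly say that the limitation is disclosed. The Blinding section states that investigator blinding is hard to maintain in this setting, adds a blinded reading and analyses only that reading. Central placement, a pre-randomisation baseline and baseline adjustment also help. This stands: it is a weakness in a stated design choice, not a contradiction or an error. The safeguards lower the risk, but as the first table shows, none closes it.

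The numerical illustration also has no direction or size from the documents. The Objectives section says that no arm has been shown superior, and its hypothesis is non-directional. That stands too. The table shows what a shift would do, not that one will occur.

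Three stronger readings are tempting, and the documents support none of them.

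- **Only one image is measured per visit.** The wording on placement is singular, but the text does not say whether the three averaged measurements come from one image or several. The acquisition concern is the same either way, because the unblinded investigator takes every image.
- **No measurement location is fixed before allocation.** The article is silent on this. How a point is relocated is detail that an article commonly leaves to the full protocol, and the baseline scan takes place before the arm is known.
- **Random placement error can be quantified.** That needs a split of measurement error between placement and reading, which the documents do not give. They also do not say whether the quoted ICC involved re-placing the probe.

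The inter-rater figure is not misdescribed: the protocol promises only to report variation between the two investigators. The risk is that a reader takes it as reliability of the whole measurement.

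**Conclusion.** The point holds as a residual risk of bias. The unblinded primary investigator takes the images and measures thickness in real time, so knowledge of the arm and of the value can influence which image is kept. The blinded re-reading and the inter-rater figure can neither reveal nor correct this.

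Its size is unknown. Under an assumed shift of 0.1 to 0.3 mm, SD 1.0 mm, 36 per arm and two-sided alpha 0.017, the pairwise false-positive rate rises from 1.7% to about 3 to 13%. A reader might infer that the thickness result is biased, or that the blinded reading is worthless. Neither follows: nothing shows that bias occurs, and the blinded reading does protect the measuring step. The change is still worth making because it is inexpensive and concerns the endpoint that sizes the trial.

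**What to change.** In the Blinding and Primary outcome measures sections:

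1. The primary investigator does not measure thickness on screen during the visit. Any inter-rater reading by that investigator is done later, from stored images.
2. At each visit, take three acquisitions with the probe lifted and re-placed each time, at the location imaged at the pre-randomisation baseline. Retain every image. The blinded assessor reads all of them, and the mean of those readings is analysed.
3. Report the inter-rater figure as agreement on reading stored images.
4. State as a limitation that an unblinded operator still handles the probe. Steps 1 and 2 reduce image selection and random placement error, but they do not remove arm-dependent placement or pressure.

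**Cost.** Some rewording, more images for the existing second investigator to read, and a few extra minutes of scanning. At an assumed one to two minutes per site and up to two sites, that is 2 to 4 minutes per visit. This is noticeable at the 1-week visit, which the Procedures section plans at no more than 10 minutes, and in a unit whose patients are mostly under 2 years old. No new staff or equipment is needed.
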